**Methods and analysis:**

Thirty residents will be recruited from an aged care facility in South Australia. The study will be conducted in two phases. In phase I, the study team will work with aged care software providers and developers of digital technologies (a wearable activity tracker and a sleep tracking sensor) to gather physical activity and sleep data, as well as medication and clinical data from the electronic medication management system and aged care clinical software. Data will be centralised into a cloud-based monitoring platform (TeleClinical Care (TCC)). The TCC will be used to create dashboards that will include longitudinal visualisations of changes in residents’ health, function and medicine use over time. In phase II, the on-site pharmacist will use the centralised TCC platform to monitor each resident’s medicine, clinical, physical activity and sleep data to identify signs of medicine-induced harms over a 12-week period.

A mixed methods process evaluation applying the RE-AIM (Reach, Effectiveness, Adoption, Implementation, Maintenance) evaluation framework will be used to assess the feasibility of the service. Outcome measures include service reach, changes in resident symptom scores (measured using the Edmonton Symptom Assessment System), number of medication adverse events detected, changes in physical activity and sleep, number of pharmacist recommendations provided, cost analysis and proportion of all pharmacists’ recommendations implemented at 4-week, 8-week and 12-week postbaseline period.

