determine the number and proportion of eligible residents who were willing to participate in the study;determine changes in resident outcomes, including changes in symptoms as measured using the Edmonton Symptom Assessment System (ESAS),^17^ physical activity and sleep (24-hour movement behaviour) and adverse events including falls (both injurious and non-injurious), fractures, delirium, faecal impaction, hospitalisation or emergency department presentation due to adverse medication events and medication incidents, predigital and postdigital pharmacist service;determine the number and types of pharmacist recommendations that resulted following use of the TCC-ADEPT platform, and the number of pharmacist recommendations that were accepted and implemented by GPs and aged care staff;explore the acceptability of the digital pharmacist service by residents and family members, aged care staff and GPs;assess the costs associated with implementing the TCC-ADEPT platform and potential cost impacts to the health and aged care system in wider-spread roll out of the platform;explore the residential aged care facility’s intention to continue to implement the pharmacist service poststudy funding and whether the service aligns to the facility’s mission or sustainability of business model.

We hypothesise that the new pharmacist service is feasible and acceptable to aged care staff, residents and their GPs, and can enhance detection of early signs and symptoms of medicine harms, triggering review and action when required.

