### Baseline data collection

Once written consent is obtained, study staff will collect baseline data from the Resident Care Assessment Record held electronically in Leecare^21^ and Medi-Map^22^ software, which contains demographic details, comorbidities, medicine use, falls history and care provided within the aged care facility. Study staff will administer the ESAS^17^ and the Montreal Cognitive Assessment (MoCA)^23^ at baseline. An observational logbook or diary will be kept to record information not collected in the existing data fields. Table 1 indicates data collected at each data collection time points.

**Table 1 T1:** Data collection schedule

Variable	Description	Data source	Data collection time points			
			Baseline	4 weeks	8 weeks	12 weeks
Demographic	Age, gender	Leecare	✓			
Medical conditions	Diagnosis of medical condition	Leecare	✓	✓	✓	✓
Medications*	Name, strength, dose, frequency of medicine administration	Medi-Map	✓	✓	✓	✓
Nutritional status	Swallowing status	Leecare	✓			✓
Functional ability	Mobilisation status	Leecare	✓			✓
Cognitive function	Montreal Cognitive Assessment	Leecare	✓			✓
Falls history	Number of falls and related health outcomes	Leecare	✓			✓
Vital signs	Height, weight, blood pressure (systolic and diastolic), respirations, pulse, BGL, SpO_2_	Leecare	✓	✓	✓	✓
Pain	PainChek score severity across six domains	Leecare	✓	✓	✓	✓
Residential Medication Management Review (RMMR)	Dates of RMMR provision will be recorded	On-site aged care pharmacist	✓	✓	✓	✓
Physical activity	Time spent in light, moderate, vigorous-intensity activity	Fibion SENS device	✓	✓	✓	✓
Sleep	Movements during sleep, durations of light, deep and REM sleep	Fibion Emfit device	✓	✓	✓	✓
Edmonton Symptom Assessment Scale	Severity across 10 symptoms	Participant or third-party informant review	✓	✓	✓	✓
Adverse events	For example, falls, fracture, delirium, faecal impaction, incontinence	Leecare, pharmacists, aged care staff, residents	✓	✓	✓	✓
Incidents	Medication incidents will be recorded including date/time and severity	Leecare, pharmacists, aged care staff, residents	✓	✓	✓	✓
Ambulance call-outs	Date and reasons will be recorded	Leecare, pharmacists, aged care staff, residents	✓	✓	✓	✓
Hospital visits	Date and reason of emergency department visits or hospital admission will be recorded	Leecare, pharmacists, aged care staff, residents	✓	✓	✓	✓
All-cause mortality	Any deaths in the 12-week study period will be recorded	Aged care staff		✓	✓	✓

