### Phase II

The pre-post feasibility study will be conducted over 12 weeks. The study will be reported according to the Consolidated Standards of Reporting Trials checklist for pilot and feasibility trials.^28^ The sleep sensor (Fibion Emfit)^19^ will be installed in the rooms of all enrolled and consenting residents, and study staff will provide residents with an activity tracker (Fibion SENS).^18^ Two weeks of baseline data will be collected from these technologies prior to the start of the pharmacist service.

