#### Process evaluation to assess the feasibility of the pharmacist service

A mixed methods evaluation, applying the RE-AIM evaluation framework^30^ will be performed to assess the feasibility of the pharmacist service. Descriptive statistics will be employed to report demographic characteristics and health information obtained from the Resident Care Assessment Record.

To determine *reach*, the number and proportion of eligible residents who were willing to participate in the study will be calculated. Information that will be collected include number of residents approached by the study staff or pharmacist and provided with the study information, number of residents who meet the inclusion criteria, number of residents who provided consent and number of participants who completed the 12-week study.

To determine *effectiveness*, changes in resident symptom score predigital and postdigital pharmacist service, as measured using the ESAS, will be assessed. Changes in medication use will be assessed, including changes to sedative and anticholinergic load predigital and postdigital pharmacist service. Changes in 24-hour movement behaviour, as measured using the activity tracker, will be assessed predigital and postdigital pharmacist service. The number of adverse events including falls (both injurious and non-injurious), fractures, delirium, faecal impaction, hospitalisation or emergency department presentation due to adverse medication events and medication incidents will be assessed. The number of adverse events experienced by residents within the 12-week predigital pharmacist service versus number of adverse events experienced during the 12-week digital pharmacist service period will be compared. Pre-post paired t-test or Wilcoxon test will be used for continuous data and McNemar’s tests for categorical variables.

To assess service *adoption*, the number and proportion of organisation staff invited, that agreed to participate, will be calculated.

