### Risks

The aim of the current study is to test the feasibility of using digital technologies to help pharmacists better monitor the effects of medicines that the residents are taking. There are no apparent risks to participants that would be expected as a result of the pharmacist service or the unintrusive activity and sleep monitors. It is anticipated that there may be direct benefits to the participants through a reduction in adverse events.

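### The comparison of adverse-event counts before and during the service is open to ascertainment bias, because capture is likely to be more complete while the service runs

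*Protocol article*

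**What the plan says.** The comparison is fixed under the effectiveness heading of the process evaluation (Protocol article, Process evaluation to assess the feasibility of the pharmacist service). One side is "The number of adverse events experienced by residents within the 12-week predigital pharmacist service versus" and the other is the "number of adverse events experienced during the 12-week digital pharmacist service period will be compared". Paired tests are named for pre-post data. The same residents serve as their own comparison, and there is no concurrent control.

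On how the data arise:

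- **Baseline data collection:** "Once written consent is obtained, study staff will collect baseline data from the Resident Care Assessment Record held electronically in Leecare" and the medication software.
- **Table 1:** the adverse-event row has one list of sources (the care record, pharmacists, staff and residents), with collection at baseline and at weeks 4, 8 and 12.
- **Phase II:** "Two weeks of baseline data will be collected from these technologies prior to the start of the pharmacist service".
- **Identification of triggers for review, and Pharmacist service:** once the service runs, a rules-based algorithm flags residents and the on-site pharmacist monitors them on the dashboard.

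On what is expected, the Introduction hypothesises that the service "can enhance detection of early signs and symptoms of medicine harms, triggering review and action when required". The Abstract lists the "number of medication adverse events detected" as an outcome. The Risks section says "there may be direct benefits to the participants through a reduction in adverse events". The listed strengths and limitations do not mention differential capture.

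**The concern.** A service designed to find medicine harm is judged partly by a count of harm, and the service itself helps to produce that count. If events are found more completely in the second period, the difference between the periods mixes two things: how many events occurred and how many were noticed. A service that prevents events could then appear to have no effect or to increase harm.

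This is the only adverse-event comparison in the article. It may inform decisions about a larger trial, so a misleading sign would matter even in a feasibility study.

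**Working it through.** **1. The two periods side by side**

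| | 12 weeks before | 12 service weeks |
|---|---|---|
| Named sources (Table 1) | care record, pharmacists, staff, residents | the same |
| Collections (Table 1) | one, at baseline | three, at weeks 4, 8 and 12 |
| Interval each collection covers | up to 12 weeks | 4 weeks |
| Dashboard and automated flags | not in service use | in use |
| Pharmacist monitoring on the dashboard | no | yes |

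The single retrospective collection is an inference; the article does not call it a look-back. It follows from baseline data being collected after consent and only two weeks of device data preceding the service. If the earlier period ends when the service starts, at least 12 − 2 = 10 of its 12 weeks (10/12 = 83%) precede the device baseline.

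**2. Formula**

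Observed ratio (service/before) = true rate ratio × capture ratio, where

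capture ratio = share of events captured during the service ÷ share captured before.

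**3. Results over assumed capture ratios**

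The article gives no capture rates, so the ratios 1.0 to 2.0 are assumptions that show a range.

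| True rate ratio | Capture 1.0 | 1.25 | 1.5 | 2.0 |
|---|---|---|---|---|
| 1.0 (no effect) | 1.00 | 1.25 | 1.50 | 2.00 |
| 0.8 (20% fewer) | 0.80 | 1.00 | 1.20 | 1.60 |
| 0.7 (30% fewer) | 0.70 | 0.875 | 1.05 | 1.40 |
| 0.5 (50% fewer) | 0.50 | 0.625 | 0.75 | 1.00 |

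A true 20% reduction vanishes at a capture ratio of 1.25 (0.8 × 1.25 = 1.00) and looks like a 20% increase at 1.5 (0.8 × 1.5 = 1.20). At 1.5 the service would have to prevent 1 − 1/1.5 = one third of events to show no change.

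**4. Scale in events**

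Inputs: 30 residents (Sample size); up to 27 adverse medicine events per 100 residents per month, and about one resident in five affected each month (Introduction). I read the second figure as 0.20 events per resident-month, although it is strictly a proportion of residents. Twelve weeks = 84/30.44 = 2.76 months.

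- Lower: 30 × 0.20 × 2.76 = 16.6 events.
- Upper: 30 × 0.27 × 2.76 = 22.4 events.

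Taking these as the counts recorded before the service, with no true effect and a capture ratio of 1.5, the comparison would be 16.6 against 24.8, or 22.4 against 33.5. These rates are for adverse medicine events, and the list of events to be compared appears broader, so the counts only indicate scale. They play no part in the ratios in step 3.

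**5. Chance of a misleading test result**

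This uses an exact two-sided 5% conditional test on two Poisson counts, which is an illustration and not the article's own test. The ranges run over the two event rates.

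| Truth | Capture ratio | Result | Chance |
|---|---|---|---|
| No effect | 1.0 | significant increase | about 2% |
| No effect | 1.5 | significant increase | 21–28% |
| No effect | 2.0 | significant increase | 61–75% |
| 30% fewer | 1.0 | significant decrease | 11–15% |
| 30% fewer | 1.5 | significant decrease | about 1% |

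**6. Where the bias sits**

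Delirium, faecal impaction, non-injurious falls, medication incidents and the judgement that a hospital visit was due to a medicine all depend on how closely someone looks. Fractures and all-cause emergency or hospital transfers depend on it little, and a capture ratio near 1 is plausible for them.

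**The case against.** The other side has a good case on several points.

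- **Sources.** A reader might infer that earlier events come from the care record alone and service events from four sources. Table 1 does not support this: the same sources are listed at baseline and at each later visit. The sentence on the care record concerns baseline data in general and does not override that row. What remains is the difference in collection frequency and the running service.
- **Attribution.** A reader might infer that events are attributed to medicines only in the service period. The section on triggers describes how the pharmacist uses the dashboard. It sets no adjudication rule for the compared counts and does not say that earlier events go unattributed.
- **Direction.** A reader might infer that the article predicts both a rise and a fall in the same count. The Introduction partly reconciles the two: undetected mild harm leads to serious events, so finding early signs and preventing later events are steps in one chain. The Abstract's wording about events detected is loose, but it does not leave the expected direction undefined.
- **Magnitude.** The ratios in the working restate assumed capture. For instance, 60–80% capture before and 90% during give 0.9/0.8 = 1.13 to 0.9/0.6 = 1.50, but no source in the article supports those shares.
- **Weight.** This is a 30-resident feasibility study, effectiveness is one of five evaluation domains, and the article ties no success criterion to this count.

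These points narrow the concern but do not remove it. Identical source labels do not give equal capture when one period is covered by a single collection without the dashboard and the other by three collections with flags and active monitoring. The pharmacist who delivers the service is also a source of the events by which it is judged.

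**Conclusion.** The concern holds in limited form. As written, the comparison mixes detection with occurrence, and the likely bias is towards a higher count during the service. Its size cannot be derived from the article. Over assumed capture ratios of 1.25 to 2.0, it would cancel a true reduction of between 20% and 50%. The conclusion rests on two things: the inference that the earlier weeks are covered by a single baseline collection, and the judgement that flags and monitoring raise capture.

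It would go too far to say that the result cannot be interpreted in either direction. Fractures, injurious falls and all-cause transfers are affected little, and a fall in the total despite better capture would still be informative about detection bias, though other weaknesses of an uncontrolled comparison would remain. The feasibility aims (reach, adoption, implementation, maintenance) are untouched. The point should be fixed, but it does not threaten the study.

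**What to change.** 1. Base the pre-post effectiveness comparison on events extracted from the routine care record (Leecare) by the same study staff, with the same form, for both 12-week periods and regardless of presumed cause.
2. Make fractures, injurious falls and all-cause emergency or hospital transfers the main comparison.
3. Report delirium, faecal impaction, non-injurious falls and medication incidents descriptively for both periods, marked as detection-sensitive.
4. Add a source field to the event form. Report events first found by the pharmacist, the dashboard or resident interview separately, as a detection outcome for the service period only, and state that a higher count there reflects detection and not harm.
5. Name differential capture among the limitations.

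The cost is outcome wording and one field on the form; recruitment, devices and care do not change. The price is that fewer events and fewer event types enter the main comparison, so it will be less precise. Some bias remains, because an active on-site pharmacist can also change what staff write in the care record.

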### Informed consent

Prior to the conduct of any study procedures, study staff will provide residents or an authorised representative with the participant information sheet and consent form. The purpose of the study and all study procedures will be discussed with the resident or an authorised representative. Informed written consent will be obtained by the resident or authorised representative. Participants will be assured that participation is completely voluntary and that they can withdraw from participation at any time.

### Data management

All identifying information will be kept in secure settings in the residential aged care facility, University of South Australia (QUMPRC) or University of New South Wales, accessible only by central study staff. Where necessary, electronic tablets used for data collection (under password protection), and hard copies of questionnaires, will be stored temporarily within the residential aged care facility. The electronic tablets and forms will be stored in locked cabinets within the facility (accessible only by study staff). Information containing identifiers will be removed at the end of data collection by the project lead. The QUMPRC physical and IT environment operates to in-confidence and protected levels according to Department of Defence security standards.

### Risks

The aim of the current study is to test the feasibility of using digital technologies to help pharmacists better monitor the effects of medicines that the residents are taking. There are no apparent risks to participants that would be expected as a result of the pharmacist service or the unintrusive activity and sleep monitors. It is anticipated that there may be direct benefits to the participants through a reduction in adverse events.

### Ethics and dissemination

Ethical approval has been obtained from the University of South Australia Human Research Ethics Committee (HREC205098). The study will be conducted in accordance with principles of the Declaration of Helsinki^35^ and the National Statement of Ethical Conduct in Human Research.^36^ During the study, any amendment to the study protocol or related documents will be submitted to the ethics committees for approval prior to implementation.

A Clinical Study Report in accordance with relevant International Council for Harmonisation of Technical Requirements for Pharmaceuticals for Human Use (ICH) guidelines will be prepared, summarising all study data and analysis. Study findings may also be published or presented at scientific meetings. All publications arising from the study will comply with recognised ethical standards concerning publications and authorships. In all instances, dissemination of the study results will include de-identified or average study data and will not identify an individual participant.

## Data Availability

No data are available. Individual participant data will not be made available due to data being collected from a small group of aged care residents located at one facility in South Australia, and the high risk of re-identification of individual participants.
